## Abstract

This study aims to assess the efficacy of a psychoeducational family intervention (PFI) to reduce the severity of depressive symptoms and to improve psychosocial functioning and to increase social contacts in a sample of patients with major depressive disorder (MDD). The degree to which PFI will reduce patients’ relapses, hospitalizations, and self-stigmatization and will improve their quality of life will also be assessed. Other secondary outcomes include the improvement of relatives’ coping strategies, family burden, expressed emotions and quality of life. This non-profit, unfunded, national, multicentric randomized controlled trial with blinded outcome assessments will be carried out in 24 Italian university outpatient units. Families will be assessed at baseline and at 6, 12, and 24 months post-randomization. Our working hypothesis is that the PFIs will reduce the patients’ severity of depressive symptoms, their relapses, and their hospitalizations, and that they will improve their psychosocial functioning and quality of life. We expect these results to be maintained after 12 and 24 months, albeit with a reduction in magnitude. The sample will consist of 384 patients randomized at a 1:1 ratio and stratified according to center, age, gender, and educational level.

## 1. Introduction

Major depressive disorder (MDD) is the most common mental disorder, with prevalence rates ranging from 7.2% to 10.8% in the general population [1]. It is a highly recurrent disorder [2], with approximately 50% of patients experiencing a relapse after a first episode, 70% after a second episode, and 90% after a third one [3].

According to the World Health Organization, MDD is among the top 10 causes of disability worldwide, and it is associated with high personal and societal costs and a significant reduction in the quality of life of both patients and their relatives [4,5].

Caring for a patient with MDD can be highly demanding and cause significant distress in family members, as is evidenced by the high rates of divorce and the frequent financial difficulties found among patients with MDD and their family members [6]. Balkaran et al. report that the levels of subjective and objective burden experienced by relatives of patients with depression are significantly higher than those reported by the families of patients with other mental disorders, including schizophrenia and bipolar disorder [7]. Relatives of patients with MDD often report financial difficulties, reduced social activity, concerns about stigma and prejudice toward people with depression and their families, and feelings of loneliness [8,9,10,11,12].

Between 40 and 70% of relatives of patients with major depression develop clinically significant anxiety and/or depressive symptoms [13,14], though these tend to recede as the severity of the depressive symptoms in their ill relatives reduce [14]. Additionally, family members often report a lack of adequate information on how to interact with their loved one [15], along with high levels of expressed emotions, in particular emotional overinvolvement and criticism [16].

The few available data about the impact of dysfunctional family environments and the long-term outcomes of MDD indicate that high levels of family burden, expressed emotions, and dysfunctional coping strategies by family members have a significant impact on the long-term outcomes of patients with major depression [17]. Heru et al. [13] and Keitner et al. [18] found that patients with MDD living in families with high levels of expressed emotion and burden achieve a full functional recovery after an acute episode less frequently than those living in less problematic families.

The available evidence shows that patients with MDD and their relatives should receive effective psychosocial interventions [19,20]. However, research on the best treatment options for MDD is scarce, and data are mainly derived from research on schizophrenia and bipolar disorder. For both of these disorders, psychoeducational family interventions (PFIs) have been shown to be particularly effective [21,22,23]. In fact, when provided to patients with schizophrenia and their family members, PFIs reduce relapses [24] and hospitalizations [25,26,27,28], and when provided to patients with bipolar disorder and their relatives, both during the acute phase [29] and in the long term [30,31], PFIs prevent relapses, reduce the number of acute episodes [32], improve patients’ adherence to pharmacological treatments [33,34], and foster psychosocial functioning [35] as well as coping strategies in their family members [36,37,38,39,40]. Based on this evidence, several international guidelines [41,42,43,44] recommend the use of PFIs in the clinical management of severe mental disorders, as well as the adoption of new delivery approaches which include modern technologies [38,39,40].

Despite the relevance of the family context to the recovery of patients with major depression [45,46], studies on the efficacy of PFIs in patients with major depression are limited. The efficacy of PFIs in patients with MDD and their relatives has been explored in only a few randomized controlled trials [47,48,49,50]. A recent metanalysis which included five RCTs found that the intervention had a small but significant effect in improving depressive symptoms [49], though the included studies had serious limitations. Thus, firm conclusions about the effectiveness of PFIs in the treatment of MDD cannot yet be drawn.

## 2. Aims

The primary aim of this study is to assess the efficacy of PFIs in a group of patients with a diagnosis of MDD in terms of: (1) reduction of depressive symptoms; (2) improvement of psychosocial functioning; and (3) increase of social contact. The efficacy of PFIs will also be evaluated in terms of: (1) reduction of relapses and hospitalizations at 18 months post-randomization; (2) improvement of adherence to pharmacological treatments and of patients’ quality of life; (3) reduction of self-stigmatization; (4) improvement of coping strategies and expressed emotion in family members, and reduction of family burden; (5) improvement of quality of life of family members. Finally, we will investigate whether the efficacy of the psychoeducational intervention is mediated by the presence of specific temperamental profiles and childhood traumas.

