### 8.3. Exploratory Outcomes

The presence of childhood traumas and certain affective temperaments (i.e., cyclothymic, irritable, and hyperthymic temperaments) can be considered possible predictors and/or mediators of response to psychosocial treatments. Thus, these risk factors will be included as possible moderators in order to assess the influence of these variables on the efficacy of the experimental intervention. Additionally, a series of clinical indicators of illness severity will be collected (including age at onset of the first episode, previous psychiatric hospitalizations, number and type of suicide attempts, alcohol and drug use, presence of psychotic symptoms during acute phases, severity of symptoms at baseline, and adherence to pharmacological treatments), and these will be used as explanative variables. Multivariable models will be corrected for these variables in order to identify patients who are more likely to be responsive to the effects of PFIs.

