### 9.2. Statistical Analyses

The statistical analyses will be conducted in accordance with the intention-to-treat analysis. Missing data will be handled using a last observation carried forward (LOCF) analysis. Descriptive statistics will be calculated for the dependent and confounding variables for both groups. Confidence intervals will be calculated at 95%.

The analytical plan will include the following: (1) the use of generalized estimating equations (GEEs), which will provide an estimation of the impact of the intervention on the primary and secondary outcomes while controlling for multiple confounders (i.e., age, gender, illness duration, number of previous relapses, severity of symptoms at baseline, previous psychiatric admissions, physical and mental comorbidities, presence of psychotic symptoms during acute phases, suicidality, pharmacological treatments); (2) the application of a structural equation model to identify possible mediators and moderators of intervention efficacy (i.e., specific temperamental profiles, the presence of childhood trauma and/or abuse, severity of symptoms at baseline, the patient’s psychosocial functioning at baseline, number of family members, the relatives’ coping strategies and levels of expressed emotions at baseline); and (3) the use of a multivariate logistic regression model to identify predictors of a poor response to the experimental intervention.

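### Temperament and childhood trauma are fixed before randomisation, so they can moderate the intervention's effect but cannot mediate it; the mediation aim cannot be answered as written

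*Protocol article*

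**What the plan says.** The protocol article gives temperament and childhood trauma three different roles.

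- **Section 2, Aims**, makes them mediators: "we will investigate whether the efficacy of the psychoeducational intervention is mediated by the presence of specific temperamental profiles and childhood traumas".
- **Section 8.3, Exploratory Outcomes**, says that they "can be considered possible predictors and/or mediators of response to psychosocial treatments". The next sentence says that "these risk factors will be included as possible moderators in order to assess the influence of these variables".
- **Section 9.2, Statistical Analyses**, plans "the application of a structural equation model to identify possible mediators and moderators of intervention efficacy". One undivided list follows. It opens with "specific temperamental profiles, the presence of childhood trauma and/or abuse, severity of symptoms at baseline" and goes on to the patient's functioning at baseline, the number of family members, and the relatives' coping and expressed emotion, both at baseline. No item is assigned to one role.
- **Section 10, Discussion**, gives the hypothesis as an influence of these traits on how responsive patients are, which describes moderation.

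Table 2 schedules the temperament scale (B-TEMPS-M) and the trauma questionnaire (CTQ) at T0 only.

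Two further statements concern who responds. Section 8.3 introduces a set of clinical indicators of illness severity and adds: "Multivariable models will be corrected for these variables in order to identify patients who are more likely to be responsive". Section 9.2 ends with "the use of a multivariate logistic regression model to identify predictors of a poor response to the experimental intervention".

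**The concern.** Mediation and moderation are different questions and need different data. A mediator lies on the path from treatment to outcome: the intervention changes it, and that change moves the outcome. A moderator is a characteristic present beforehand that makes the effect larger or smaller. A family intervention given to adults cannot alter whether they were traumatised as children, and with a single T0 measurement the trial would hold no later value of either trait.

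An analysis that follows the Aims literally would return a null result or a chance finding. Either could be misread: the null as evidence that these traits do not matter for the intervention, the chance finding as a mechanism. The Discussion presents mediators and moderators of this intervention as a novelty of the study, so this is a conclusion that readers will look for.

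The sentence in 8.3 on correcting models has a related weakness. Adjusting for severity indicators as main effects shows who does better or worse overall. By itself it does not show who gains more from the intervention.

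**Working it through.** The plan states no figure on this point, so there is none to reproduce. The check has three parts.

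**1. Could any listed variable be a mediator?** The list in 9.2 is set against the timing in the article.

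| Variable in 9.2 | Value used | Can treatment have changed it? |
|---|---|---|
| Temperament (B-TEMPS-M) | T0 only (Table 2) | No |
| Childhood trauma (CTQ) | T0 only (Table 2) | No |
| Symptom severity | Baseline (9.2) | No |
| Psychosocial functioning | Baseline (9.2) | No |
| Number of family members | No later time point given | Not as listed |
| Relatives' coping | Baseline (9.2) | No |
| Relatives' expressed emotion | Baseline (9.2) | No |

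Table 2 shows that relatives' coping (FCQ) and expressed emotion (LEE) are also collected at T1, T2 and T3, but 9.2 lists only their baseline values.

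**2. The indirect effect.** Let M be a variable fixed before randomisation and Y the outcome.

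- Path from arm to variable: a = E[M | PFI] − E[M | control]. Under the 1:1 randomisation of section 3, a = 0 in expectation.
- Indirect effect as a product of coefficients: a × b = 0 × b = 0, whatever the effect b of M on Y.
- More generally, the indirect effect is the sum over m of E[Y | arm, m] × (P(m | PFI) − P(m | control)). The bracket is zero in expectation, so the result also holds when arm and M interact.

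**3. What each test would show if moderation were real.** The following inputs are assumptions and are not in the documents: a binary trait with prevalence 20%, 30% or 50%; Y = −0.5 × arm + 0.5 × trait + 0.5 × arm × trait + noise with SD 1; no clustering; 3,000 runs per setting. The intervention effect is then −0.5 SD without the trait and −0.5 + 0.5 = 0 with it. The totals 176 and 384 are those in section 9.1.

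| Prevalence | N | Mean a | Mean a × b | Mediation test significant | Interaction test significant |
|---|---|---|---|---|---|
| 20% | 176 | −0.0011 | 0.0008 | 4.8% | 25% |
| 20% | 384 | −0.0003 | 0.0005 | 4.9% | 50% |
| 30% | 176 | −0.0017 | −0.0001 | 5.4% | 34% |
| 30% | 384 | 0.0003 | 0.0009 | 4.8% | 62% |
| 50% | 176 | −0.0010 | −0.0006 | 6.2% | 39% |
| 50% | 384 | 0.0014 | 0.0011 | 4.0% | 69% |

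The mediation test required both paths to be significant at 5%. It fires at about its nominal error rate and gains nothing from the larger sample, because it responds only to chance imbalance.

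The same model shows why main-effect adjustment does not identify responders. Without the interaction term it gives a single intervention effect for everyone, about −0.5 + 0.5 × prevalence: −0.40, −0.35 and −0.25 SD at 20%, 30% and 50%. The true effects of −0.5 and 0 in the two subgroups are not visible in it.

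**The case against.** The strongest reply is that this is a slip of terminology. Section 8.3 says that the traits will enter as moderators, the Discussion frames the question as responsiveness, and 9.2 assigns no variable to either role. A structural equation model can test moderation through interaction terms or a multi-group comparison. The analyses are exploratory and the primary comparison does not depend on them.

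Most of this stands, and it limits the point. It does not remove it: the Aims state a mediation question outright, and 9.2 offers no variable that could answer one. A full analysis plan that followed the Aims would inherit the error.

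A reader might infer several stronger things that the article does not support:

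- *That every baseline variable in 9.2 will be tested as a mediator.* The list covers both roles, and only temperament and trauma are named as mediators elsewhere.
- *That 8.3 will correct for temperament and trauma in order to find responders.* That sentence refers most directly to the clinical severity indicators.
- *That the logistic model will be fitted to the PFI arm alone, or with main effects only.* The article gives neither the fitting population nor the terms, and such detail is commonly left to an analysis plan.
- *That family burden and adherence are listed as baseline values only in the structural equation model.* They are not in that list at all.
- *That about 30% of such trials would show a false mediator, from 1 − 0.95^7 = 0.30.* This concerns the arm-to-variable path alone, which is not a full mediation test. It assumes seven independent variables, although severity and functioning, for example, are plausibly correlated.

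**Conclusion.** The point holds. The mediation aim for temperament and childhood trauma is wrong as written: the indirect effect is zero in expectation by design, and no post-randomisation variable is named that could replace these traits. The article is also inconsistent across sections 2, 8.3, 9.2 and 10 about the role they play.

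The zero rests only on randomisation and on the variables being fixed beforehand. The simulated rates rest on the assumed prevalences and effect sizes and ignore clustering by centre. They show that a mediation test would be uninformative where an interaction test has some power, though limited power; they do not predict what this trial will find.

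The remark on adjustment in 8.3 is narrower: it applies if the severity indicators enter as main effects only. What is at stake is an exploratory aim and a claimed novelty.

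**What to change.** - **Aims, 8.3 and 9.2:** describe temperament, childhood trauma and the other listed baseline variables as moderators throughout, in line with the Discussion.
- **9.2:** test each by an arm-by-baseline-variable interaction, or an equivalent multi-group comparison in the structural equation model, using both arms. Keep these tests exploratory because their power is limited.
- **8.3:** where the purpose is to identify likely responders by the severity indicators, specify interactions with arm as well as adjustment.
- **Logistic model in 9.2:** if it is meant to show who responds to the intervention, and not simply who has a poor outcome, include both arms and the interaction. Otherwise describe it as a model of prognosis.
- **Mediators:** delete the term unless post-randomisation variables are named. If mediation is wanted, T1 values of relatives' coping (FCQ) and expressed emotion (LEE), adjusted for T0 and related to a later outcome, would give the right time order. This is optional.

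The moderation changes are mainly wording, plus interaction terms in models already planned, and need no new data. The optional mediation analysis would use measurements already scheduled, but it is an additional analysis to specify.

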**Family Coping Questionnaire (FCQ) [56]**	**Coping strategies**	**The FCQ is a self-administered questionnaire consisting of 34 items rated using a 4-point scale, from 1 (never) to 4 (always). The items can be grouped into the following 11 subscales: seeking information on a patient’s illness, positive communication toward the patient, relatives’ maintenance of social interests, patient’s involvement in social activities, talking with friends about the patient’s condition, coercion, avoidance, resignation, use of alcohol and drugs, collusion, and searching for spiritual help. A higher score is indicative of a stronger endorsement of each coping strategy.**	**Relatives**	**T0, T1, T2, and T3**

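### The variables listed for mediation in Sections 2 and 9.2 are pre-randomisation characteristics, which can only be moderators or predictors; the changeable family variables collected at T1 are not named as mediators

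*Protocol article*

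**What the plan says.** Section 2 (Aims) ends with an aim on temperament and childhood trauma: "we will investigate whether the efficacy of the psychoeducational intervention is mediated by the presence of specific temperamental profiles and childhood traumas".

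Section 9.2 names the tool as "the application of a structural equation model to identify possible mediators and moderators of intervention efficacy". One list, introduced by *i.e.*, serves both roles. It begins with "specific temperamental profiles, the presence of childhood trauma and/or abuse, severity of symptoms at baseline", continues with the patient's psychosocial functioning at baseline, and ends with "number of family members, the relatives’ coping strategies and levels of expressed emotions at baseline". The list does not say which variable has which role.

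Section 8.3 says that temperament and trauma "can be considered possible predictors and/or mediators of response to psychosocial treatments", and in the next sentence that "these risk factors will be included as possible moderators". Section 10 (Discussion) presents the study of mediators and moderators as a novelty, but words the hypothesis as an influence of temperament and trauma on how patients respond to family treatment.

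Table 2 schedules the temperament scale (B-TEMPS-M) and the trauma questionnaire (CTQ) at T0 only. Relatives' coping (FCQ), expressed emotion (LEE), family burden (FPQ) and medication adherence (Morisky) are scheduled at T0, T1, T2 and T3.

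**The concern.** Mediation and moderation are different questions with different models. A mediator lies on the path from arm to outcome: the arm changes it, and it then changes the outcome. A moderator is present beforehand and alters the size of the arm effect. The first is estimated as an indirect effect, the second as an arm-by-variable interaction.

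Childhood trauma, temperament measured once at T0, and baseline values of severity, functioning, coping and expressed emotion all precede the intervention. They can moderate or predict, but they cannot mediate. If the mediation part of the model is fitted to them, it has nothing true to find, and a positive result would be a chance imbalance in a prognostic factor presented as a mechanism.

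Meanwhile, the variables that the intervention is expected to change (Sections 2 and 8.2) are collected after baseline. Coping and expressed emotion enter the Section 9.2 list only as baseline values. Burden and adherence are not in it.

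**Working it through.** The plan gives no figure for this point, so there is none to reproduce. The check compares the lists with the visit schedule and then illustrates the consequence.

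**Step 1. Timing of each listed variable (Section 9.2 against Table 2)**

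| Variable | Time point | Can the arm change it? |
|---|---|---|
| Temperament | T0 only | No |
| Childhood trauma | T0 only, past events | No |
| Symptom severity | At baseline | No |
| Psychosocial functioning | At baseline | No |
| Number of family members | Not stated | Not a target of the intervention |
| Relatives' coping | At baseline, on the natural reading | No |
| Relatives' expressed emotion | At baseline | No |

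The coping row rests on the phrase "coping strategies and levels of expressed emotions at baseline", in which I take the qualifier to cover both items. I also take T0 to precede allocation, as the order of steps in Section 3 suggests.

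**Step 2. The indirect effect**

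Indirect effect = a × b, where a is the effect of arm on the variable and b is the slope of outcome on the variable given arm. For a variable fixed before randomisation, a = 0 by design. So a × b = 0 whatever b is.

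**Step 3. Illustration by simulation**

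Inputs from the protocol: 384 patients, 1:1 (Sections 3 and 9.1). Assumed, in SD units: arm effect −0.3 and b = 0.4; for a baseline variable, interaction 0.3; for a post-baseline variable, a = 0.4 and no interaction. There were 5000 runs. Mediation was declared when both paths were significant at two-sided 5%.

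| Variable | Mean indirect effect | Mediation declared | Interaction declared |
|---|---|---|---|
| Baseline | 0.000 (SD 0.056) | 5.0% | 82.8% |
| Post-baseline, shifted by arm | 0.160 (true 0.4 × 0.4 = 0.16) | 97.7% | 5.3% |

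The 5.0% in the first row is the false-positive rate. The 82.8% shows that the same baseline variable is informative when tested as a moderator.

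**Step 4. Size of a spurious indirect effect**

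SD = slope × 2/√384 = slope × 0.102. For slopes of 0.2 to 0.5 this is 0.020 to 0.051 SD, so the 95% range is from ±0.04 (1.96 × 0.020) to ±0.10 (1.96 × 0.051) SD.

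**Step 5. If all seven were tested as mediators**

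The plan does not say that they will be. For independent, prognostic variables tested without multiplicity control, the chance of at least one false mediator is at most 1 − 0.95^7 = 0.302. Simulation gave 0.261 to 0.285 for inter-correlations of 0.4 down to 0.

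**Step 6. A mediator that could be found**

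With 15% dropout, 384 × 0.85 ≈ 326. Power ≈ Φ(a√(n/4) − 1.96) × Φ(b√n − 1.96).

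- a = 0.3, b = 0.2: Φ(0.75) × Φ(1.65) = 0.735
- a = 0.4, b = 0.3: Φ(1.65) × Φ(3.46) = 0.950

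The values of a and b are assumptions.

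**The case against.** The strongest reply is that this is a slip of terminology. Section 8.3 says that temperament and trauma enter as moderators, and Section 10 words the hypothesis as responsiveness to treatment. T0-only measurement is right for that question. This stands. A reader might infer that the whole aim cannot be answered, but the documents do not support that: the moderation question can be answered with the planned data.

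A second reply is that the Section 9.2 list also serves moderation, and that nothing says each member will be tested as a mediator. This also stands. A reader might infer that the trial will report false mechanisms at the rate in step 5, but that rate depends on an analysis the protocol does not describe. What remains is that no member of the list is a valid mediator, so the mediation half has no content.

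Third, *i.e.* need not mean that the list is exhaustive. Sections 8.3 and 10 name further explanatory variables, such as age at onset and suicide attempts, and Section 8.3 includes adherence without a time point. That is fair, but none of these is named as a mediator.

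Fourth, Section 2 sets no aim to test family processes as a mechanism, so the trial cannot be faulted for missing one. That is right. The T1 variables matter only if the mediation claim is kept.

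Finally, technical detail may belong in an analysis plan that is not shown. But the article itself fixes the aim and the list, and a plan that followed them would inherit the problem.

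**Conclusion.** The point holds in a limited form. Section 2 uses *mediated* for variables that can only moderate or predict, Section 8.3 gives them both roles within two sentences, and Section 9.2 names no valid mediator. The zero indirect effect follows from randomisation, given that T0 precedes allocation, that the baseline qualifier covers coping, and that number of family members is not altered by the intervention. The simulated error rates and powers are illustrations under assumed path values, not properties of the plan.

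The consequence is confined to an exploratory aim. The primary and secondary comparisons, the sample size and the visit schedule are not affected. It should still be corrected, because the article presents the study of mediators as a novelty and the correction is cheap.

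**What to change.** - **Section 2:** replace *mediated by* with *moderated by* for temperament and childhood trauma.
- **Section 8.3:** drop the word *mediators* for these variables so that it agrees with the sentence that follows it.
- **Section 9.2, item 2:** split the list. Name the baseline variables as moderators, tested by arm-by-variable interaction, and state that the baseline qualifier applies to coping as well as to expressed emotion.
- **If mediation is kept:** name T1 coping (FCQ), expressed emotion (LEE), burden (FPQ) and adherence (Morisky), each adjusted for its T0 value, as candidate mediators of patient outcomes at T2 or T3, so that the mediator precedes the outcome. Report the results as exploratory, with the caveat that the mediator-to-outcome path is not randomised and may be confounded.
- **If mediation is not kept:** remove the word from Sections 9.2 and 10.

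The cost is a change of wording and, if mediation is kept, a little more analysis. Table 2 already schedules all four instruments at the visits needed, so no patients or visits are added.
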